**Blood pressure targets and drug therapy**

Clinic BP measurements performed over a 3-month period immediately prior to entry to study will be used to calculate average Clinic BP percentile. All subjects participating in the study (with or without anti-hypertensive/s) will be randomly assigned to either 'aggressive' or 'standard' BP target study arms. All subjects will have clinic BP maintained in the assigned target range over the duration of the study. Up or down titration of blood pressure during the trial will be performed as per flowcharts in **Appendix 3**. This will be monitored at least 4-monthly at the time of routine hospital visits. Patients already on anti-hypertensive medications at the time of study entry will continue on these or change as per clinical indication. ACEi or ARB's will be the mandatory first line agents. The dose of the agent will be adjusted to achieve the target blood-pressure levels with initial follow up at 2-4 weekly intervals following commencement of medication. The following order of escalation will be used (1) calcium channel blocker (CCB) (2) beta-receptor blocker (3) others such as diuretic or an alpha channel blockers. The preferential use of long acting drugs with once daily dosing would be recommended. This order of escalation will be used unless there are clear clinical indications for other agents. Amendments to the 'BP titration' procedures (**Appendix 3**) will be made if necessary following review of data after 20 subjects.

**Also see Figures in Appendix 1: 26/01/2012 version 1**

## **2 Trial Objectives, Design and Statistics**

### **2.1. Trial Objectives**

*This should comprise specific statements of the purpose (ie aims and objectives) of the study, together with a definition of the primary (and secondary) endpoints of the study.*

*(See also 4.1.1 and 4.1.2 of this protocol)*

#### **Primary objectives**

1. a) Examine the relationship of LVM, IMT and arterial stiffness to blood pressure (following adjustment for confounders) in a cohort of children with and without CKD.  
b) Compare these measures in children with and without CKD when adjusted for peripheral and central blood pressure.
2. Perform a randomised controlled trial to determine whether aggressive blood pressure reduction (below the 40th percentile) compared to standard care (below the 75th percentile) is effective in normalising left ventricular mass, arterial structure/function.

**Secondary objectives** will be to examine the effects of aggressive versus standard blood pressure reduction on microalbuminuria and progression of renal failure and to determine if biomarkers of arterial injury/ventricular load are independently related to cardiovascular target organ damage.

### **2.2 Trial Design & Flowchart (Appendix 2)**

*A description of the design of trial to be conducted (eg double-blind, single-blind, open label, placebo-controlled, parallel-group, double-dummy, cross-over, etc.) should be given. Please also include a schematic diagram (flow chart) of trial procedures and stages is desirable as it is particularly useful for determining activities involved during each clinic visit (eg blood tests or scans, treatment, diary completion, adverse event monitoring, physical examination etc).*

The principal outcome measure for the controlled trial will be the differences in LV mass between aggressive and standard treatment groups.

Differences in IMT and PWV will be secondary outcome measures.

### **2.3 Trial Flowchart**

*Please include a time/event matrix (flow chart) of trial procedures and stages. This desirable as it is particularly useful for determining activities involved during each clinic visit (eg blood tests or scans, treatment, diary completion, adverse event monitoring, physical examination etc).*

**Please see Appendix 2 26/01/2012 version 1 with this document**

Key task completion date (months)

|                                              | Day 1                                 | 4-mths | 8-mth | 1 year | 2 year | 3 year |
|----------------------------------------------|---------------------------------------|--------|-------|--------|--------|--------|
| Patient information and informed consent     | Over first 12 months of study         |        |       |        |        |        |
| Physical examination                         | At recruitment and at least 4 monthly |        |       |        |        |        |
| Demographics                                 | √                                     | √      | √     | √      | √      | √      |
| Clinic BP and review of medications          | √                                     |        |       | √      | √      | √      |
| ABPM (in sub-group)                          | √                                     |        |       | √      | √      | √      |
| Central BP evaluation                        | √                                     |        |       | √      | √      | √      |
| Blood sample                                 | √                                     |        |       | √      | √      | √      |
| Urine sample                                 | √                                     |        |       | √      | √      | √      |
| Non-invasive arterial studies (cIMT and PWV) | √                                     |        |       | √      | √      | √      |
| Echocardiography                             | √                                     |        |       | √      | √      | √      |
| 24-hour ambulatory BP monitoring             | √                                     |        |       | √      | √      | √      |

All subjects will have clinic BP maintained in the assigned target range over the duration of the study. Up or down titration of blood pressure during the trial will be performed as per flowcharts in **Appendix 3**. Amendments to the 'BP titration' procedures (appendix 3) will be made if necessary following review of data after 20 subjects.

## 2.4 Trial Statistics

*A description of the measures taken to avoid, or at least minimize, bias should be given. Specifically, this normally means describing the procedure(s) for randomisation and blinding. A description of the statistical methods to be employed, including timing of any planned interim analyses should also be provided. The number of subjects to be enrolled (in multicentre trials, the numbers of subjects for each site) should be stated, together with the rationale for the sample size (the "power calculation"). The level of significance that is to be used in each trial analysis must be stipulated, together with the procedure(s) for accounting for any missing, unused, and spurious data. Procedures for reporting any deviation from the original statistical plan should be described and justified. The data set for any analysis must be clearly stipulated (eg "all subjects", "randomised subjects", "intent to treat") and the population(s) should be clearly defined.*

Differences in outcome will be estimated using a random effects (mixed) model that includes the baseline value of the outcome. Sensitivity analyses will be performed to also include key prognostic variables including known factors other than blood pressure and those identified by univariate analyses.

### 2.4.1 Sample Size

The outcome data are longitudinal and so we will fit a model that takes account of this data structure. The random effects model is a 2-level multilevel model that allows for the repeated data within subjects, while allowing some measurements to be missing. (This is preferred to repeated measures analysis of variance that requires complete data on all subjects). For a particular outcome, eg LVmass, the baseline value for each subject will be included in the model to adjust for (random) baseline variability between subjects. The results of the analysis are in the form of mean difference in LVmass between the intervention and control groups, at the endpoint, with a 95% CI.

The original sample size calculations were based upon longitudinal measurements of LVMI at annual intervals in our cohort of children with CKD (n=47). The SD of change in LVMI is 7.7 g/m2.7 and this was obtained without the same standardized reading of LVM that we are proposed in the study. To be conservative we assume just a 20% improvement on our existing data giving an SD of 6 g/m2.7 result from our own cohort. Thus with n=60 in each group we should be able to

detect a difference in change in LVMI of  $> 3.1 \text{ g/m}^{2.7}$  (=9% of baseline LVMI) over the 2 year duration with 90% power ( $P<0.05$ ). This is one third of the difference ( $9.4 \text{ g/m}^{2.7}$ ) between subjects in our cohort that have blood pressure in the 50-75th and below 40th percentiles. Although we are assuming relatively rapid tracking of LV mass in relation to blood pressure, this is not unreasonable given the time frame of LV regression in adults. A recent meta-analysis [Fagard et al, *Hypertension* 2009; 54:1084] of randomized studies shows a mean change in LVMI of 10.3% over duration of 6 months.

Interim analysis to be performed at 1-year by the statistical team to check if the SD of measured indexed LV mass (LVMI) is in keeping with initial projections. The choice of standard deviation (SD) for the initial sample size was made using the best data available at the time of the study design. In accordance with good practice, we will monitor the SD during the study across the whole study group i.e. NOT by randomised group. In this way we can verify that the overall SD observed in the trial is in fact as expected. If the SD is found to be very different, either larger or smaller, we will consider whether the sample size calculations need to be revised accordingly. In this way we will be able to be as certain as is possible that the trial is powered as planned and ensure that the primary study endpoint is achieved. We will inform the Research Ethics Committee of the results of the interim analysis soon after the end of the 1st year.

With regard to PWV, the within subject SD for measurements separated by several months is 0.5 m/s so we should be able to detect a difference in change in PWV of 0.3 m/s. Although we do not have data relating PWV to level of blood pressure, this difference is small in absolute terms (being equivalent to only a few years of “vascular ageing” in adults) and therefore we feel it is likely that we will be able to detect a meaningful change in PWV.

The following research team members will be ‘blinded’ to the blood pressure percentile of the patient: (i) technologist/s performing the cardiac and vascular measurements and (ii) Research team member entering data to MedSciNet. The clinical team will also be kept blinded to the results of the echocardiogram and vascular studies.

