| Sample Size                             | 150 (to give n=120 complete) and n=150 age matched controls                                                                                                                                                                                            |
| Summary of eligibility criteria         | Inclusion criteria:
aged 2 to 15 years with CKD (stages 1-4 in the last 12 months)
+/- anti-hypertensive/s medications (irrespective of recent change/s in anti-hypertensive therapy) with none of the exclusion criteria outlined below. |
| Version and date of final protocol      | Version 1 23/03/2012                                                                                                                                                                                                                                   |
| Version and date of protocol amendments | Version 1.2 20/07/2014                                                                                                                                                                                                                                 |

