#### 1.2 *Trial design including blinding*

Interventional multi-centre RCT UK-wide national trial with a sample size of 144 patients.

The following research team members will be 'blinded' to the blood pressure percentile of the patient: (i) technologist/s performing the cardiac and vascular measurements and (ii) Research team member entering data to MedSciNet. The clinical team will also be kept blinded to the results of the echocardiogram findings.

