### **1.8 Sample size estimation (including clinical significance)**

The original sample size calculations were based upon longitudinal measurements of LVMI at annual intervals in our cohort of children with CKD ( $n=47$ ). The SD of change in LVMI is  $7.7 \text{ g}/\text{m}^{2.7}$  and this was obtained without the same standardized reading of LVM that we are proposed in the study. To be conservative we assume just a 20% improvement on our existing data giving an SD of  $6 \text{ g}/\text{m}^{2.7}$  result from our own cohort. Thus with  $n=60$  in each group we should be able to detect a difference in change in LVMI of  $> 3.1 \text{ g}/\text{m}^{2.7}$  ( $=9\%$  of baseline LVMI) over the 2 year duration with 90% power ( $P<0.05$ ). This is one third of the difference ( $9.4 \text{ g}/\text{m}^{2.7}$ ) between subjects in our cohort that have blood pressure in the 50-75th and below 40th percentiles. Although we are assuming relatively rapid tracking of LV mass in relation to blood pressure, this is not unreasonable given the time frame of LV regression in adults. A recent meta-analysis [Fagard et al, Hypertension 2009; 54:1084] of randomized studies shows a mean change in LVMI of 10.3% over duration of 6 months.

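### The sample-size statement claims 90% power for a 3.1 g/m^2.7 difference in LVMI change, but its own inputs give about 81%

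*Combined protocol and SAP*

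**What the plan says.** Protocol section 2.4.1 (Sample Size) starts from an SD of annual change in LVMI of 7.7 g/m^2.7, seen in the investigators' own cohort of 47 children with CKD. It expects standardised reading of the echocardiograms to reduce this: "To be conservative we assume just a 20% improvement on our existing data giving an SD of 6" g/m^2.7. It continues: "Thus with n=60 in each group we should be able to" detect a difference in change of more than 3.1 g/m^2.7, described as "9% of baseline LVMI) over the 2 year duration with 90% power", at P<0.05.

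SAP section 1.8 carries the calculation over unchanged, including "over the 2 year duration with 90% power". The 60 per group are completers: the Study Synopsis gives the number of children with CKD as "150 (to give n=120 complete".

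Neither section says whether the test is one- or two-sided. Protocol 2.4.1 and SAP 1.9 report the result as a mean difference with a 95% confidence interval, which corresponds to a two-sided 5% test. No one-sided test appears in either document.

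**The concern.** Group size, SD, difference, significance level and power are all stated, so any four fix the fifth. They do not agree. A difference of 3.1 with SD 6 and 60 per group fits 80% power almost exactly, yet the label is 90%.

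This is the power statement for the primary outcome, and both governing documents carry it. A reader of a null result would take it that a true difference of 3.1 g/m^2.7 had only a 10% chance of being missed. On the stated inputs that chance is about 19%.

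The 1-year interim check (protocol 2.4.1, SAP 3.2) would not catch the error. It compares the observed SD with the projection, so an SD confirmed at exactly 6 would appear to endorse 90% power.

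**Working it through.** **Inputs**

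- n = 60 per group, SD of change 6, difference 3.1 g/m^2.7, P<0.05, stated power 90% (protocol 2.4.1; SAP 1.8).
- Two-sided 5%, inferred from the 95% confidence interval (protocol 2.4.1; SAP 1.9).
- 1:1 allocation (SAP 1.5).
- SD of change 7.7 in the earlier cohort (protocol 2.4.1).
- SD of LVMI at one time point: 10.1 and 8.1 in the two arms at baseline (Table S2), and 9.1 in the cohort described in protocol section 1.

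**1. Attempt to reproduce the stated 90%**

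Standard error of the difference = SD × √(2/n) = 6 × √(2/60) = 1.095.

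Power = Φ(3.1/1.095 − 1.960) = Φ(2.830 − 1.960) = Φ(0.870) = 80.8%. The exact noncentral t calculation gives 80.1%. The 90% is not reproduced.

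**2. What the printed figures do match**

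Detectable difference = (1.960 + z for power) × 1.095:

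- 80% power: (1.960 + 0.842) × 1.095 = 3.07, which rounds to the printed 3.1.
- 90% power: (1.960 + 1.282) × 1.095 = 3.55.

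Group size for a difference of 3.1 = 2 × 6² × (1.960 + z for power)² / 3.1²:

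- 80% power: 58.8, so 59 per group, next to the printed 60.
- 90% power: 78.7, so 79 per group.

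The SD that would give 90% power at 3.1 with 60 per group is 3.1 / (3.242 × √(2/60)) = 5.24.

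**3. Other readings that might give 90%**

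| Reading | Power for the difference |
|---|---|
| One-sided 5%, 60 per group | 88.2% (exact t 87.9%) |
| 75 per group (all 150), two-sided | 88.6% (exact t 88.2%) |
| Difference of one third of 9.4 (3.13) | 81.6% |
| Difference of 9% of the cohort mean of 37.8 (3.4) | 87.4% |

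None reaches 90%. The first conflicts with the 95% interval, and the second with the text, which ties the power to 60 per group. The last two replace the printed 3.1.

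**4. Baseline adjustment**

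Assume the same SD, σ, at baseline and follow-up, with correlation ρ. Then SD of change² = 2σ²(1 − ρ), and the baseline-adjusted variance is SD of change² × (1 + ρ)/2. With SD of change 6, ρ = 1 − 18/σ².

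- σ = 8.1: ρ = 0.726, adjusted SD = √(36 × 0.863) = 5.57, power = Φ(3.047 − 1.960) = 86.1%.
- σ = 10.1: ρ = 0.824, adjusted SD = √(36 × 0.912) = 5.73, power = Φ(2.964 − 1.960) = 84.2%.

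**5. No improvement in reading (SD 7.7)**

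Standard error = 7.7 × √(2/60) = 1.406. Power = Φ(2.205 − 1.960) = 59.7% (exact t 59.0%). The detectable difference is 3.94 at 80% power and 4.56 at 90%.

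**The case against.** The strongest defence is that 81% belongs to a plain two-sample comparison of change, which is not the planned analysis. The protocol plans a mixed model that includes the baseline value and uses repeated measurements, and SAP 3.1 compares annual rates of change. Such a model may well be more efficient, and the calculation above puts baseline adjustment alone at about 84-86%. This part stands: under the planned analysis the shortfall may be nearer 4 to 6 points than 9. It does not rescue the statement, because the documents give no correlation or variance gain in the sample-size calculation and name only SD 6. The power of the slope comparison cannot be derived from the figures given, so it can neither confirm nor refute 90%. For the same reason, a reader should not infer that the planned analysis has a 19% miss rate; that figure belongs to the simple comparison.

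A second defence is that the SD is an openly stated assumption. It was to be reviewed at 1 year without splitting by arm, with possible revision of the sample size. That is fair, and it answers criticism of the choice of 6; the gap between 6 and an exact 20% cut (7.7 × 0.8 = 6.16) is rounding. It does not answer the mismatch, which is present even when the SD is exactly 6.

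A third is that the supplement already reports results for 124 randomised children, so interpretation rests on confidence intervals rather than planned power. That lowers the urgency but leaves the statement wrong.

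**Conclusion.** The stated power is wrong as written in both sections. On the documents' own inputs, with a two-sided 5% test of mean change, it is about 81% rather than 90%, and the difference detectable at 90% power is about 3.55 rather than 3.1 g/m^2.7. The printed figures fit an 80% calculation, but the documents do not show whether the slip lies in the power, the difference or the group size. Two-sidedness is inferred from the 95% interval. The 84-86% for baseline adjustment assumes equal variance over time and a baseline SD of 8.1-10.1.

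Three stronger readings are not supported:

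- **That the trial had about 60% power.** The SD of 7.7 comes from the earlier cohort, read without the trial's standardised method. The documents do not report the trial's own SD of change in LVMI, so 60% is a scenario only.
- **That power can be recomputed from the year-2 numbers in Figure S6.** Those counts belong to the z-score results, and the mixed model uses all visits rather than a year-2 completer comparison.
- **That the PWV statement contains the same error.** The text says "the within subject SD for measurements separated by several months is 0.5 m/s" and attaches no power to the 0.3 m/s. If 0.5 is already the SD of change, 0.3 m/s has about 91% power with 60 per group.

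**What to change.** In protocol section 2.4.1 and SAP section 1.8, the authors should check which of the power, the difference and the group size was meant, make the figures agree, and state the sidedness. If 60 completers per group and SD 6 stand, suitable wording would be: about 80% power to detect 3.1 g/m^2.7, or 90% power to detect about 3.6 g/m^2.7, with 60 completers per group and an SD of change of 6 (two-sided 5%).

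Add one sensitivity line for SD 7.7: about 60% power for 3.1 g/m^2.7, with a detectable difference of about 3.9 at 80% power and 4.6 at 90%. If the authors relied on a gain from baseline adjustment or repeated measures, they should state the correlation assumed and show the calculation.

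The cost is wording in two places. The design, the analysis and the number of patients do not change. The only downside is a less favourable stated figure.

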## **2.4.2 Randomisation**

Randomisation will be performed using the Institute of Psychiatry CTU online platform. Following consent baseline measurements will be performed immediately *before* randomisation. At external centres visiting investigators will perform measurements immediately before randomisation.

## **2.4.3 Analysis**

As outlined above.

(i) Appointment of ‘Data Monitoring Committee’ (DMC). The members of this committee will include independent observers as per routine guidelines. The DMC will review the results of the proposed interim analysis at 1-year following commencement of study.

(ii) Interim analysis will also review data regarding the safety of proposed study arms at 1-year. The results will be reviewed by DMC and used to inform REC and the wider research team.

(iii) Both SPSSv17 and SigmaStat v10 will be used for statistical analysis, in close consultation with statisticians at Kings College London.

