## EXPERIMENTAL DESIGN AND METHODS

### Protocol

**Subjects** (n=150, to give n=120 complete) will be aged 2 to 15 years with CKD stages 1-4 in the last 12 months. Subjects will be eligible to enter the study whilst on anti-hypertensive/s medications irrespective of recent change/s in anti-hypertensive therapy. Detailed inclusion and exclusion criteria are described later in this document under 'Section 3'. Subjects with arterio-venous fistulae, on dialysis or those with a previous kidney transplant at the time of study entry will be excluded. eGFR will be

calculated using the Schwartz formula and CKD staged as per existing definitions [31,32]. Patients who reach end stage renal failure and commence dialysis or receive a kidney transplant will stop participating in the 'randomised controlled trial' but continue to have measurements performed until the end of the study. Informed consent/assent will be obtained from parents and patients (if age applicable) for participation in the study, as per institutional ethics committee approval. A control group (n=120) of age matched children without CKD will be included with all proposed study related investigations to be performed at baseline and at annual intervals. These will be recruited from siblings of study subjects and from a local community using links from a school based liaison project. In addition we aim to recruit a further control group (n=30) of subjects with systolic BP <50th percentile but on no anti-hypertensive medication.

All study related investigations at 'baseline' will be performed just before randomisation. Following enrolment and performance of baseline investigations children with CKD will be randomised to the two arms of the study: aggressive BP control (below the 40th percentile) or standard BP control (between 50th-75th percentile). A minimisation procedure will be used to ensure that patients randomised to the two arms are matched for: age, gender, CKD stage and proteinuria. Children will be recruited over the first 12-months of the study and will therefore have at least 2-years of follow up. Following randomisation all children in whom blood pressure is not to target will be reviewed at 2-4 weekly intervals. Thereafter all children will be monitored at least 4-monthly at the time of routine hospital visits and have clinic BP maintained in the assigned target range over the duration of the study.

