### **Analysis:**

- (i) [name], Professor of Medical Statistics, King's College London and her team will provide high level statistical input to the trial, overseeing the randomisation and formulating the analysis plan. Differences in outcome will be compared by a random effects (mixed) model. [name] will formulate a detailed analysis plan during the work-up phase of the study.
- (ii) Interim analysis to be performed at 1-year by statistical team to check if SD of measured indexed LV mass (LVMI) is in keeping with initial projections.
- (iii) Appointment of 'Drug monitoring committee' (DMC). The members of this committee will include independent observers as per routine standards. The DMC will review the results of the proposed interim analysis at 1-year following commencement of study.

- (iv) Interim analysis will also review data regarding the safety of proposed study arms at 1-year. The results will be reviewed by DMC and used to inform REC and the wider research team.

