#### 1.5 Method of allocation of groups

After informed consent was obtained and eligibility confirmed, participants were randomised by the chief investigator using a rapid, secure, web-based randomisation system developed by the Kings Clinical Trial Unit, London. Randomisation to standard or intensive treatment arms (1:1) was stratified according to clinical centre.

In this open-label multi-centre trial participants and recruiting clinicians were informed of the participant's allocation and trial related systolic BP targets electronically. Therefore, no unblinding or code breaking is required. Further, those performing investigations were blind to participants SBP percentile and target, and the trial team and recruiters blinded to results.

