### **3.2 Interim analysis**

Interim analysis to be performed at 1-year by the statistical team to check if the SD of measured indexed LV mass (LVMI) is in keeping with initial projections. The choice of standard deviation (SD) for the initial sample size was made using the best data available at the time of the study design. In accordance with good practice, we will monitor the SD during the study across the whole study group i.e. NOT by randomised group. In this way we can verify that the overall SD observed in the trial is in fact as expected. If the SD is found to be very different, either larger or smaller, we will consider whether the sample size calculations need to be revised accordingly. In this way we will be able to be as certain as is possible that the trial is powered as planned and ensure that the primary study endpoint is achieved. We will inform the Research Ethics Committee of the results of the interim analysis soon after the end of the 1st year.

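### The release rule for the 1-year interim safety results lets by-arm data pass beyond the DMC to an undefined research team in an open-label trial

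*Combined protocol and SAP*

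**What the plan says.** The 1-year interim has two parts.

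- **SD check.** Protocol section 2.4.1 and SAP section 3.2 compare the SD of LVMI with the planning value. This part is pooled: "we will monitor the SD during the study across the whole study group i.e. NOT by randomised group".
- **Safety review.** Protocol section 2.4.3 (ii) and section 9, Analysis (iv), add: "Interim analysis will also review data regarding the safety of proposed study arms at 1-year". Both continue: "The results will be reviewed by DMC and used to inform REC and the wider research team".

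The clock is study time, not patient time: "The DMC will review the results of the proposed interim analysis at 1-year following commencement of study".

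The trial is open label. SAP section 1.5 says that "participants and recruiting clinicians were informed of the participant's allocation" and BP target, and that the chief investigator performed the randomisation. On treatment, the protocol says: "The dose of the agent will be adjusted to achieve the target blood-pressure levels". Section 3.3 has children withdrawn for adverse effects that are found concerning. Section 5.2 has the local principal investigator assign causality and expectedness.

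Elsewhere the DMC's output is described differently. The Data and Safety Monitoring Plan in section 5.2 has it advise the management committee and an independent steering committee on whether continuing is safe. Section 6 then fills the steering committee with the chief investigator, co-applicants, research staff and the trial statistician.

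**The concern.** A review of the safety of the study arms is naturally a comparison by arm. The release sentence takes the results themselves as its subject, not a recommendation drawn from them, and sends them to a group that no section defines. The plan applies a pooling safeguard to the SD and blinds the clinical team to echo and vascular results, but it sets no matching limit on the safety comparison.

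Investigators who have seen an early imbalance, even a chance one, could titrate less firmly, withdraw children sooner or attribute more events to treatment in the arm that looks worse. Three things would be exposed:

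- the BP contrast between arms;
- the SAP's assumption (section 3.1.1) that data lost to withdrawal are missing at random;
- the by-arm adverse event summary (SAP section 2.3).

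The last is sensitive because one paragraph of section 5.2 limits reporting to events judged to be reactions. For non-serious events, a causality judgement can therefore decide whether the event is counted.

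**Working it through.** The plan states no figure on this point, so there is none to reproduce. The check has three parts.

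**1. Does any section close the gap?**

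- Sections 2.4.1 and SAP 3.2: the pooling rule covers only the SD of LVMI.
- SAP 3.2: contains no safety review and names only the REC as recipient of interim results. It neither repeats nor restricts the protocol's rule.
- SAP 1.5: says the trial team and recruiters are blind to results. In context these are the results of the investigations, not safety data.
- Section 5.2, monitoring plan: describes DMC output as advice, which points to a narrower release, but does not say that only advice leaves the DMC.
- Section 6: the body receiving that advice consists of investigators and trial staff, so it is no barrier.

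No section requires a closed report or restricts release to pooled data or a recommendation.

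**2. How much follow-up comes after release?**

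Inputs: 150 children (sample size), and the timetable "Children will be recruited over the first 12-months of the study and will therefore have at least 2-years of follow up". Twelve months of recruitment plus 24 months gives a close at about month 36. Assumption: uniform accrual, so mean entry is at month 6.

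Mean total follow-up = 36 − 6 = 30 months = 2.5 years, and 150 × 2.5 = 375 child-years.

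Accrued by release at month m = 150 × (m − 6)/12.

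| Release | Child-years accrued | Still to come | Share |
|---|---|---|---|
| Month 12 | 150 × 0.50 = 75 | 300 | 300/375 = 80% |
| Month 15 | 150 × 0.75 = 112.5 | 262.5 | 262.5/375 = 70% |
| Month 18 | 150 × 1.00 = 150 | 225 | 225/375 = 60% |

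The share does not depend on the number of children. Sensitivity:

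- *Fixed two years each:* (2.0 − 0.5)/2.0 = 75% at month 12 and (2.0 − 1.0)/2.0 = 50% at month 18.
- *Dropout:* the plan expects 150 to give 120. In the least favourable case all 30 leave at the moment of release. Month 12: 120 × 2 = 240 still to come, 240/(75 + 240) = 76%. Month 18: 120 × 1.5 = 180, 180/(150 + 180) = 55%.
- *Calendar time:* 24/36 = 67% at month 12 and 18/36 = 50% at month 18.

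**3. How noisy would early results be?**

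Suppose nine events fall with equal probability in either arm (an illustration, not a plan figure). A split of 6–3 or more extreme, in either direction, has probability 2 × (84 + 36 + 9 + 1)/512 = 260/512 = 51%. An imbalance that looks meaningful at one year could easily be chance.

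**The case against.** **Only conclusions may have been meant.** A reader might infer that treating clinicians will know the arm comparison. The documents do not support that as fact. The recipients are undefined, no section says a between-arm table leaves the DMC, and the monitoring plan describes advice. The protocol also distinguishes research team members, some of them blinded to BP percentile, from the clinical team. This stands: by-arm release is permitted by the wording, not shown to be planned.

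**The primary measurement is protected.** Echo studies are read by one investigator blinded to medical history, and clinicians are blinded to echo and vascular results. This also stands. Titration follows flowcharts, which limits discretion there but not in withdrawal or causality.

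**Open-label investigators already see their patients' events.** They do, but Table S4 spreads 124 children over 14 centres, 13 of them with 12 or fewer. Local experience is not the aggregate comparison.

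**Table S3 might be read as evidence of harm.** Stops of 18/64 against 10/60 invite that reading. The total includes eGFR below 15 (3 v 3), relocation (1 v 1) and unknown cause (1 v 2). The P value is 0.13, and no stop is dated relative to the interim. A lower BP target could produce such a gap with no disclosure at all, so the figure is not evidence for this point.

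**Loss of effect.** One might also infer a specific reduction in the detectable LVMI difference. The documents give no basis for how much BP separation would be lost, so none is claimed.

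**Conclusion.** The point holds as a defect in a stated release rule. Two protocol sections send the 1-year arm-safety results past the DMC without limiting them to pooled data or a recommendation, and no other section supplies the limit. Under uniform accrual and a close at month 36, about 60% to 80% of planned child-years would follow a release between months 18 and 12. The top figure needs release with no delay. Late release with a fixed two years each, or with early dropout, brings the share down to 50% to 55%.

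The risk runs through BP separation, dropout and safety attribution. Its size in LVMI units cannot be derived from the documents, and nothing shows that it materialised. This is a cheap improvement worth making, not a flaw that undermines the primary comparison.

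**What to change.** Amend protocol section 2.4.3 (ii) and section 9, Analysis (iv), along these lines:

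*By-arm safety data are presented only to the DMC, in a closed report. The research team, including the steering committee, receives the DMC's recommendation and safety figures for both arms combined, unless the DMC judges that wider release is needed to protect participants. The DMC may report to the REC as it or the REC requires.*

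The last sentence leaves the ethics committee's access open. Confining it to pooled data in a paediatric trial would be contestable and is not needed here.

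Reconcile this with the Data and Safety Monitoring Plan, with section 6 (the steering committee is called independent but is made up of investigators and staff) and with SAP section 3.2, which omits the safety review. Because outcome tables already accompany the plan, the sponsor should also state what was released at one year and to whom.

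The cost is a short amendment and a separate closed report. Investigators would see less interim detail. Sample size and treatment rules are unchanged.
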